## Abstract

**Background:**

Farm and rural youth have frequent exposure to hazardous noise on the farm and recreationally, and have an increased prevalence of noise-induced hearing loss. There is a lack of programs to prepare this high-risk population to use hearing conservation strategies.

**Methods:**

The purpose of this project is to test innovative hearing health education programs delivered to a large target group and to determine the effectiveness and sustainability of these programs in promoting hearing health among farm and rural youth. Specifically, this project includes: a) an interactive face-to-face informational program alone, b) an interactive face-to-face informational program followed by an Internet-based booster, and c) a no-intervention control. Sites will include selected affiliates of a major farm youth safety education organization. Data will be collected at baseline, 3, and 12 months. A linear mixed model will be used to compare the effectiveness of the three interventions over time. Descriptive statistics will be used to compare program costs and sustainability ratings.

**Discussion:**

Outcomes of this project will provide knowledge necessary to implement quality and cost-effective services to farm and rural youth, a high-risk and underserved population, that can be implemented and sustained after the study is completed.

**Trial registration:**

Clinicaltrials.gov NCT02472821 Registered 09 Jun, 2015.

## Background

Noise-induced hearing loss is a highly prevalent, permanent, irreversible condition that disproportionately impacts the future quality of life of farm and rural youth, their families, and communities. An estimated 2 million children and adolescents younger than 20 years of age are exposed to farm hazards as farm residents, farm family workers, hired workers, children of migrant or seasonal workers, or farm visitors resided on farms in 2010 [1]. Farm operators experience frequent exposure to high noise and among the highest prevalence rates of hearing loss among all categories of workers [2]. Similarly, farm and rural children have frequent exposure to high farm noise; [3] farm youth are engaged in farm tasks from an early age [4, 5]. In addition to their farm noise exposure, farm youth are exposed to high recreational noise (e.g., firearms, ATVs, and personal listening devices). Farm youth have lower hearing ability than their urban peers [6, 7].

Noise-induced hearing loss (NIHL) is permanent, irreversible, and insidious. Noise-induced hearing loss is characterized by loss of hearing in higher frequencies. The condition is permanent and incurable, and typically progresses slowly and insidiously with continued exposure to high levels of noise. Most people are unaware that they are affected until it is already moderately severe [8].

NIHL has a negative impact on the quality of life of the affected individuals as well as their families and communities. It affects physical and emotional functioning, social life, and employment. In addition, NIHL results in heavy social and economic burdens on families and communities from all ethnic and socioeconomic groups. In addition, persons with NIHL usually live with a lifetime *of* tinnitus, and have increased safety risks due to difficulty hearing warning sounds [9]. Monetary costs for NIHL are high, and include workers’ compensation (for employees) and medical costs [10]. Importantly, hearing loss has also been associated with increased risk for injury among farmers [11].

The significant features of the proposed studies are listed as follows:*The proposed study maximizes the opportunity for success by focusing on primary prevention of hearing loss among youth.* Because NIHL is permanent and irreversible, treatments are limited to hearing aids for sound amplification. Most users find hearing aids expensive, unlike their natural hearing, and particularly unsatisfactory when there is background noise or when trying to focus on one speaker when there are other competing sounds [12]. The proposed study aims to change hearing health behavior from a young age, before the onset of noise-induced hearing loss, and before these youth add to the already high public health burden of persons with hearing loss [13].*The proposed study tests the effectiveness of new evidence-based programs to protect a high-risk and underserved population of rural and farm youth from NIHL.* Farmers are a unique population. Unlike workers in general industry, family-owned farms with fewer than 11 employees are not protected by OSHA or its Hearing Conservation Standard (i.e., noise level monitoring, hearing conservation program, audiometric testing, training, provision of hearing protection devices) [14, 15]. It is also legal for minors younger than age 12 to be employed on a farm [16].*The proposed study addresses barriers to use of hearing conservation strategies specific to rural and farm youth.* In a recent focus group study, farm youth reported that they were universally exposed to hazardous noise on the farm and in recreational activities,that perceived barriers to use of hearing conservation strategies outweighed the perceived benefits, and they lacked an association between their use of hearing conservation strategies today and their hearing ability later in life (invincibility). Noise elimination is the most preferred method of prevention of NIHL. However, this approach is often not technically or economically feasible in the farm work environment [17].*The proposed study tests the sustainability of programs to protect rural and farm youth from noise-induced hearing loss.* Programs can continue to deliver benefits when they are sustainable, i.e., able to maintain programming and its benefits over time.*The proposed study addresses the strategic goals of relevant federal agencies to reduce* noise-induced hearing loss and accompanying tinnitus, including Healthy People 2020, [18] NIDCD, [19, 20] NIOSH, [21] the National Agriculture, Forestry, and Fishing Agenda, [21] OSHA, [22] the North American Guidelines for Children’s Agricultural Tasks, [23] and IOM [24].*The proposed study addresses barriers to adoption of evidence-based interventions that have been shown to be efficacious and effective.* Small-scale hearing conservation programs for farm and non-farm youth have been successful in changing HPD use behavior over short time periods, and offer confidence in the potential for maximizing the impact on health by changing behavior before the onset of noise-induced hearing loss, [5, 25–29] but effectiveness of these programs is limited by lack of systems to deliver programs widely to at-risk youth, and at an effective frequency to maintain change over time [25, 28, 30].*The proposed study takes advantage of existing infrastructure.* The study involves partnering with well-established and culturally relevant systems that serve the health and safety educational needs of farm and rural youth (Progressive Agriculture Foundation Safety Day and Dangerous Decibels virtual exhibit). PAF does not currently offer hearing health education, but this new partnership will serve to add hearing health education to the already existing system designed to deliver health and safety educational programming to 98,000 rural youth and adults annually.*The proposed study tests the effectiveness of a booster intervention to effect the desired public health impact.* Previous RCT studies examining the use of boosters on adult hearing protector use [31] have had mixed results, demonstrating the need for further research exploring the effects of the powerful intervention in this behavioral context among youth.

### Theoretical framework

Schell and colleagues [32] have developed a model for measuring eight organizational and contextual domains which best ensure that program outcomes can be realized over time [https://sustaintool.org/assess]. The proposed study seeks to assess the sustainability of hearing health education programs (with and without Internet boosters) using Schell’s model.

In addition, the intervention will be guided by the Model of Effects on Predictors of Intent to Use Hearing Conservation Strategies Intervention (Fig. 1).

**Fig. 1 Fig1:**
[figure not shown]
Intervention Effects on Use of Hearing Conservation Strategies

Although hearing conservation programs for farm and non-farm youth have been successful in changing hearing protector use, [5, 25, 27–30] effectiveness of programs is limited by lack of reach to at-risk youth, and effective doses [25, 28, 30]. The proposed study uses an established educational system (Safety Day) to deliver hearing health education to youth, and will determine the most effective and sustainable approach to hearing health education among farm and rural youth.

This project will result in identification of the effectiveness, costs, and sustainability estimates associated with each approach to hearing health education among farm and rural youth. Cost-effective and sustainable hearing health education programs are expected to have the greatest impact on reducing rates of noise-induced hearing loss, tinnitus, and other negative effects of high noise exposure, and improving quality of life in this high-risk and underserved group.

This study maximizes opportunity for a sustainable impact on public health by building on a well-established educational program, Safety Day. Ongoing activities in the Safety Day (exclusive of this study) include recruiting, training, and administering consents; the study activities will incrementally increase activities in these areas, leading to a high level of efficiency.

The proposed study tests an under-tested intervention approach: the booster. Previous randomized clinical trial (RCT) studies examining the use of boosters on hearing protector use [31, 33, 34] have had ambiguous results, pointing to the need for further study of this promising approach.

The proposed study addresses long-standing problems with hearing health education programs which have not been addressed by previous effectiveness studies, i.e., access and program sustainability. The proposed study also uses a previously-established, tested, [28] free-to-use Internet program (Dangerous Decibels® virtual exhibit) not previously tested for use among farm and rural youth.

The proposed study uses a strong (RCT) scientific design. Information from this stronger study design will provide more generalizable evidence useful in the future development of hearing conservation programs and health policy, resulting in enhanced opportunity to impact the public’s health.

## Methods and design

A team of multidisciplinary members with diverse expertise has been formed to accomplish the study aims. Areas of expertise include: 1) development and testing of programs designed to increase use of hearing protection devices among farmers, 2) farm youth safety education, 3) analysis of hearing health education programs, 4) health program cost analysis, 5) assessment of public health program sustainability, and 6) Web hosting and user monitoring.

The purpose of this project is to compare the effectiveness and sustainability of new programs designed to increase hearing conservation practices (e.g., use of HPDs, turn it down, walk away) among farm and rural youth, thereby reducing noise-induced hearing loss, and involves a partnership with the Progressive Agriculture Foundation. Specifically, the study uses a cluster randomized-control design to compare two programs (with a control) for effectiveness and sustainability: a community-based interactive youth educational program alone (Group A); and a community-based interactive youth educational program followed by an Internet-based booster (Group B). Both programs will be delivered through the Progressive Agriculture Foundation (PAF) Safety Day program.

Safety Days are one-day, hands-on workshops that teach farm children safe farm practices. Each year, Safety Days reach more than 98,000 children and adults in over 400 sites across the United States and Canada. These fun, interactive, and hands-on learning experiences result in increased knowledge about safety, as well as positive change in safety behavior [35–38]. The intervention will also use the Dangerous Decibels® virtual exhibit (DDVE) an Internet-based educational program *targeted to youth* offered through Oregon Health Sciences University and partners. The DDVE will be used as *a* booster in the proposed study.

### Interventions

The study aims to test alternative hearing health education programs, and determine their effectiveness and sustainability for farm and rural youth.

Intervention A consists of the interactive face-to-face hearing conservation program developed by the project team. It consists of discovery-based, developmentally appropriate activities designed to teach common farm and recreational sources of hazardous noise, effects of hazardous noise on ear structure and function, and age-appropriate ways to protect oneself, e.g., walk away, turn it down, and wear protection. The 20-minute lesson includes student involvement in demonstrations and visuals, demonstration and supervised practice in insertion of a child-safe hearing protection device, provision of a sample hearing protector, and elements relevant to the rural and farm community (e.g., common farm noise sources). In a preliminary test with 64 fourth grade students, comparison of pre- and post-test results showed changes of scores in the desired direction, and pre-post-test differences were statistically significant*.* In addition, results of the pilot test suggested that overall, the pilot program was acceptable to school officials and students, instruments were reliable and valid, and the brief educational program is feasible.

Training in use of the face-to-face hearing health lesson plan will be provided to selected local safety program coordinators through face-to-face and virtual train-the-trainer sessions conducted by study personnel, and a written lesson plan; the Study Coordinator will also reach out to instructors by offering individualized training and consultation. Coordinators will prepare instructors, include the lesson in their local program, and complete surveys. The hearing health lesson includes use of easily accessible teaching materials, e.g., paper-based visual aids, locally-sourced noisy equipment (e.g. electric leaf blower), pipe cleaners, and a sound meter.

Intervention B consists of an Internet-based educational booster. The Internet-based booster reinforces Intervention A content through use of the Dangerous Decibels® virtual exhibit (DDVE), an existing online educational program consisting of eight activities (www.dangerousdecibels.org/exhibit/virtual-exhibit/). The booster is developmentally appropriate, focuses on sources of sounds, consequences of noise exposure, and prevention of hearing loss. In a study testing the effectiveness of the DDVE site when used alone, students showed improvement in knowledge immediately after the intervention, although improvements were not sustained after 3 months. The Internet-based booster is a user-driven activity where students explore a variety of learning activities at their own pace. Highly interactive game-based activities include rating noise sources (e.g., lawn mower) as safe or dangerous, determining the best course of action (i.e., turn it down, walk away, wear hearing protection) in a variety of noisy situations, and choosing a course of action when confronted with social non-support of use of hearing protection. A computer (with Macromedia Flash® and Shockwave®) and Internet connection (e.g., at home, school, or public library) is required for participation.

The study design includes three arms: an interactive a face-to-face Safety Day lesson alone (Group A), a face-to-face interactive lesson followed by an Internet-based booster (Group B), and a no-invention control (Group C, Fig. 2). The Internet booster will be delivered to eligible participants following completion of the three month survey.

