#### Intervention effectiveness evaluation

After obtaining parental informed consent and soliciting the assent of child participants, pre- and post-intervention data will be collected from youths. Pre-test data will be collected via pencil-and-paper survey forms prior to the delivery of content. Three- and 12-month post-test data will be collected via the youth’s preferred communication medium following the booster intervention. Instrument means, standard deviations, and alpha coefficients are summarized in Table 2.

**Table 2 Tab2:** Timetable of project activities and benchmarks for success

Activity	Year 1 months						Year 2 months						Year 3 months						Year 4 months		
	1/2	3/4	5/6	7/8	9/10	11/12	13/14	15/16	17/18	19/20	21/22	23/24	25/26	27/28	29/30	31/32	33/34	35/36	37/38	39/40	41/42
Recruit, enroll & randomize 36 sites	X	X	X	X																	
Train coordinators (Groups A,B); & distribute materials (Groups A,B,C)		X	X	X	X	X															
Recruit 24 instructors; enroll youth; collect baseline data; deliver interactive program (Groups A,B)					X	X	X	X													
Distribute, collect 3-month surveys (Groups A,B)					X	X	X	X	X	X											
Distribute booster reminders (Group B)							X	X	X	X	X	X									
Collect 12-month surveys; distribute incentives (Groups A,B,C)											X	X	X	X	X	X					
Complete sustainability assessment														X							
Analyze data															X	X	X				
Submit progress reports						X						X						X			X
Disseminate & submit manuscripts																			X	X	X

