The primary measure to assess effectiveness is the 6 item scale of intention to use hearing conservation strategies (including turning down the volume, moving away from the noise, and using hearing protection devices such as ear plugs). The knowledge scale and the scale of interpersonal influences will also be examined. All individuals will be asked to assess these measures before intervention (baseline), and at 3 months and 12 months after the intervention. Since the cluster randomized design will be used to assign interventions and repeated measurements will be collected from the same individuals, linear mixed effects model will be used to investigate the effect of the interventions. The outcome variable is the scale of intention to use hearing conservation strategies. The important/main fixed effect is a categorical variable identifying the type of interventions. In addition, demographics variables will be included in the mixed model as fixed effects to increase the precision of estimates. The random effect in the model is the *site* variable. More precisely, we will use random intercept model for the *site* variable. We assume the site variable follows a normal distribution with mean zero and is independent to the error terms in the mixed model. The hypothesis is that there will be a significant effect of hearing intervention on the use of hearing conservation strategies and the intervention group will have higher use of hearing conservation strategies than the control group. If the effect of intervention is significant, follow up descriptive statistics on mean intent by time by treatment group will allow us to describe the effects, for example to determine whether each treatment led to more improvement in intent to use than the control condition and how big those effects were. Further tests within this analysis will compare the effects of the two interactive hearing interventions on youth.

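### The protocol contradicts itself on whether the 3-month survey precedes the booster, and the planned B-versus-A test names no time point, so read literally it can average the booster effect with waves that precede the booster

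*Protocol article*

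**What the plan says.** **Order of booster and 3-month survey.** The Interventions section of the protocol article says: "The Internet booster will be delivered to eligible participants following completion of the three month survey". The Intervention effectiveness evaluation section says: "Three- and 12-month post-test data will be collected via the youth’s preferred communication medium following the booster intervention". In Table 2, the 3-month surveys for Groups A and B run from months 9/10 to 19/20, and the Group B booster reminders run from months 13/14 to 23/24.

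**Analysis.** The Statistical analysis section (Aim 1) sets three measurement waves: "All individuals will be asked to assess these measures before intervention (baseline), and at 3 months and 12 months after the intervention". For the mixed model it states: "The important/main fixed effect is a categorical variable identifying the type of interventions". It adds that "demographics variables will be included in the mixed model as fixed effects to increase the precision of estimates", and it includes a random intercept for site. It names neither a time term nor an intervention-by-time term. Means by time and treatment group appear only as descriptive follow-up, conditional on a significant intervention effect. On the booster comparison it says: "Further tests within this analysis will compare the effects of the two interactive hearing interventions on youth". No time point is attached. The same section calls the comparison of the two programmes a secondary component of Aim 1.

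**The concern.** Groups A and B differ only in the booster. Whether Group B's 3-month score is taken before or after the booster decides what that score can say about it, and the article gives both answers.

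If the survey comes first, A and B have had the same programme at baseline and at 3 months, and only the 12-month wave carries information on the booster. A treatment coefficient that is constant over time averages that wave with waves where the true B-A difference is zero. A null result could then be read as showing that the booster adds nothing, when the test was largely looking at data collected before it.

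The article presents the booster as an under-tested approach and a significant feature of the study, so this comparison matters although it is secondary. Under Aim 2, the cost-to-effect ratio also depends on the effectiveness result.

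**Working it through.** **1. The protocol's own power figure.** Inputs from Power and sample size justification: d = 0.48, two-sided alpha 0.05, 36 sites divided equally among three arms (12 per arm), 16 youths per site, ICC 0.10.

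- Design effect = 1 + (16 - 1) × 0.10 = 2.5
- Effective n per arm = 12 × 16 / 2.5 = 76.8
- SE = √(2 / 76.8) = 0.161
- Noncentral t with 24 - 2 = 22 df: power 81.1%

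This reproduces the stated 80%. That figure is for either intervention against control at one time point, and this point does not affect it. The document claims no power for B versus A.

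**2. Table 2 against the two texts.** Baseline collection and the lesson start in months 9/10, so the first sites reach 3 months at about months 12 to 13. Booster reminders start in months 13/14. The reminder row starts and ends four months after the 3-month-survey row. This fits the Interventions section. It is not proof, because the rows overlap and record reminders, not booster use.

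**3. What a time-constant coefficient estimates.** Let δ be the B-A booster effect at waves after the booster and 0 at waves before it. With balanced waves, arm assigned by site and a site random intercept, the expected B-A coefficient is the plain average of the wave-specific differences. Adding a time main effect does not change this.

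| Order | Outcomes: baseline, 3 and 12 months | Outcomes: 3 and 12 months only |
|---|---|---|
| Survey before booster (Interventions section) | (0 + 0 + δ)/3 = 0.333δ | (0 + δ)/2 = 0.5δ |
| Survey after booster (Intervention effectiveness evaluation) | (0 + δ + δ)/3 = 0.667δ | (δ + δ)/2 = δ |

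The second row assumes the same δ at both follow-ups. With an intervention-by-time term and a 12-month contrast, the estimate is δ in every case.

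**4. Illustrative power, survey before booster.** Assumptions: δ = 0.48 SD, borrowed from the intervention-versus-control calculation because no booster effect is given; within-person correlation r between waves of 0.3 to 0.7, also not given; site variance 0.10 constant over waves; residual variance 0.90; 16 per site. For k waves averaged:

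SE = √[(2/12) × (0.10 + 0.90 × (1 + (k - 1)r) / (16k))]

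| Contrast | Expected value | SE, r = 0.3 to 0.7 | Power |
|---|---|---|---|
| Three waves pooled | 0.48/3 = 0.16 | 0.147 to 0.156 | 18% to 17% |
| Two post-tests pooled | 0.48/2 = 0.24 | 0.151 to 0.157 | 33% to 31% |
| 12 months only | 0.48 | 0.161 | 81% |

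If the site variance is split 0.08 constant plus 0.02 varying by wave, with r = 0.5, the three-wave figure is about 19%. The three-wave range is therefore about 17-19%.

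**The case against.** The strongest reply is that no sentence says B versus A is tested as an all-wave main effect. The text promises only further tests within the analysis, and the Abstract says the model compares the interventions over time. A condensed article may leave the exact contrast to an analysis plan that is not shown. This stands in part: a reader might infer that the booster effect will in fact be cut to a third, and the document does not support that as a settled result.

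It does not dispose of the point. The article goes beyond silence: it names a time-constant treatment term and assigns time by treatment to descriptive statistics. The Abstract's phrase fixes no term or contrast. A plan that tested B versus A at 12 months would be adding something the article's model description lacks.

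A second reply is that the timing conflict may be a loosely attached phrase that suits only the 12-month wave, as Table 2 suggests. That is plausible, but the two sentences still disagree about the 3-month survey and need to be made consistent.

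Third, the 0.48 booster effect is borrowed and the comparison is secondary. Both are true, so the power figures are illustrative and show no failure of a stated power claim.

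**Conclusion.** Two things hold. First, the Interventions and Intervention effectiveness evaluation sections contradict each other on whether the 3-month survey precedes the booster. Second, the model as described does not isolate the only wave that can show a booster effect if the survey comes first.

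The size is conditional. The one-third figure requires the survey before the booster, all three waves as outcomes, balanced data and no intervention-by-time term; changing the order or the outcome set moves it as tabulated above. The power figures rest further on the assumed booster effect and variance components.

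A reader might also infer that a diluted result would distort the sustainability comparison. The document does not support that: Aim 3 compares questionnaire ratings between A and B and uses no effectiveness result. Only the Aim 2 cost-to-effect ratio depends on effectiveness.

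The change is worth making because B versus A is a stated component of Aim 1 and the remedy costs almost nothing.

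**What to change.** 1. Reconcile the Interventions and Intervention effectiveness evaluation sections so that both give the same order of booster and 3-month survey, and check Table 2 against the result.
2. Add an intervention-by-time term (with its time main effect) to the Aim 1 mixed model, and define B versus A as the 12-month contrast. That wave follows the booster under either text.
3. If the 3-month survey is confirmed to precede the booster, adjust the 12-month B-A contrast for the baseline and 3-month scores. Both are then pre-booster values already collected in A and B. Do this by modelling the 12-month score with the two earlier scores as covariates, since a score cannot be outcome and covariate in the same fit. Do not adjust comparisons with Group C for the 3-month score, which follows the lesson in A and B.

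The cost is a text correction, one added interaction and a little analysis work. No new data are needed.
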